**Utilization**
Physician visits	Number of primary care or hypertension specialist visits over 12 months (patient reported).	Alberta Health Ambulatory Care Case Costing (utilizing National Ambulatory Care Reporting System)	Telemonitoring ± case management may reduce need for physician visits for BP management, scenarios tested in SA.	
Emergency department visits	Number of emergency room visits over 12 months attributable to BP or complications of treatment	Alberta Schedule of Benefits	Study may be underpowered to detect emergency department visits. Safety end points will be examined and likely resource use for each safety end point will be estimated.	
Hospitalizations	Number of hospitalizations over 12 months attributable to BP or complications of treatment	Alberta Health administrative data		
Societal costs	Patient and caregiver time costs for physician visits, emergency department visits, out of pocket medication costs. May also include data/mobile phone costs (explored in sensitivity analysis).	Standard Alberta wage rates (human capital approach)	Explored using a societal perspective.	

^a^BP: blood pressure

The 6- and 12-month follow-up data (measured as described previously) will be (1) clinical end points and patient-centered outcomes (as described previously): 24-hr ABPM, automated BP (seated, lying, and standing as described previously), telemonitored home BP, heart rate, medications, anthropomorphics, cardiovascular risk factors and markers (A1c, lipids, smoking, urinary albumin), cognition, frailty score, health care use (physician visits, emergency department visits and hospitalizations ascertained through self-report and via linked administrative health care data), quality of life and utilities, satisfaction with medical care, and depression and anxiety. (2) safety end points includes the frequency of (a) nonmechanical falls, syncope, hypotension requiring third-party assistance or medical attention and (b) electrolyte disturbances (hypokalemia [<3.3 mmol/L], hyperkalemia [>5.0 mmol/L], and hyponatremia [<130 mmol/L]. In addition, potentially life-threatening adverse effects will trigger an immediate alert causing the study team to notify the Data and Safety Monitoring Board, which will act independent of the study team to contact the patient and arrange appropriate nonstudy medical follow-up. Triggers for DSMB follow-up will include a BP ≥220/110 mmHg or a SBP <70 mmHg; potassium level ≤2.7 or ≥5.5 mmol/L; sodium level ≤126 or ≥152 mmol/L; or a PHQ-8 score ≥15, indicating severe depression. (3) User acceptability: will consist primarily of qualitative data collection. In addition, two 10-point Likert scales evaluating usability and acceptability will be collected. (4) Costing data: costing will adhere to the three-step microcosting technique of identification, measurement, and valuation of relevant health care and non–health care resources [51,52] and are outlined below and in Table 2. Resource use by category, including program start-up costs and on-going costs for each study arm, will be tabulated. In a 10% random sample of patients, time-motion studies related to the case manager will be conducted. The cost per patient will be calculated, and where any uncertainty in resource use or costs exists, plausible ranges of resource use will be determined and tested in sensitivity analysis. Resource use and cost data will be used to determine the overall and per-patient total costs, and incremental costs of interventions (telemonitoring ± case management) compared with usual care will be calculated [51,52].

### Analytic Plan for Major Outcomes

#### Aim 1: Effectiveness of Telemonitoring ± Protocolized Case Management

All primary analyses will be conducted according to the intention-to-treat principle. The primary outcome is the 1-year change in proportion of patients with overall 24-hour SBP in the optimal range (SBP is used because it is a stronger predictor of risk and because diastolic BP is rarely elevated in seniors [10]). We will use 24-hour ABPM because it is the gold-standard measurement method and the best validated clinical trial BP end point [40]. The 24-hr ABPM therapeutic range will be 110-129 mmHg in patients aged 65-79 years and 110-139 mmHg in those ≥ 80 years. Justification for the upper thresholds chosen is based on current guidelines that specify an overall 24-hour ABPM of ≥130 mmHg as high in all patients, including those with diabetes [6]. In patients ≥80 years, we will allow the option of a higher 24-hour target of <140 mmHg (ambulatory BP threshold definitions of normal versus high are lower than office BP thresholds; therefore, this threshold is analogous to the Canadian guideline concordant <150 mmHg office BP target that is allowed in older frailer patients [6]).

Major secondary outcomes will include the change in mean 24-hour SBP and diastolic BP (overall, daytime, and nighttime). Home BP and the automated BP measurements taken at each study visit will be examined similarly. Additional major outcomes will include postural BP changes and changes in A1c, lipids, anthropomorphic indices, quality of life, depression/anxiety, satisfaction with medical care, resource utilization, and the safety end points described previously.

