**Results:**

Outcomes will be ascertained at 6 and 12 months. Within-study-arm change scores will be calculated and compared between study arms. These include: (1) clinical outcomes: proportion of subjects with a mean 24-hour ambulatory systolic BP in the optimal range (110-129 mmHg in patients 65-79 years and 110-139 mmHg in those ≥80 years: primary outcome); additional ambulatory and home BP outcomes; A1c and lipid profile; medications, cognition, health care use, cardiovascular events, and mortality. (2) Safety outcomes: number of serious episodes of hypotension, syncope, falls, and electrolyte disturbances (requiring third party assistance or medical attention). (3) Humanistic outcomes: quality of life, satisfaction, and medication adherence. (4) Economic outcomes: incremental costs, incremental cost-utility, and cost per mmHg change in BP of telemonitoring ± case management compared with usual care (health payor and societal perspectives). (5) Intervention usability and acceptability to patients and providers.

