##### Data Analysis

First, variables will be examined descriptively and graphically, including assessments of temporal trends and tests of normality. Second, the 6-month and 1-year mean change from baseline in each outcome will be calculated and compared between study arms (each intervention arm to the control arm, then between intervention arms) using chi-square tests for dichotomous outcomes and unpaired *t*-tests for continuous outcomes. Third, multivariable predictors of the 1-year change in a given outcome will be identified using appropriately constructed and calibrated logistic regression models for dichotomous outcomes (including the primary outcome) or linear regression models for continuous ones. Initial models will adjust for age, sex, SBP, and residential site (eg, Greater Edmonton Foundation versus Rosedale). Examples of additional covariates that may be examined include sociodemographic variables, comorbidities, baseline medications, primary care physician, and tests of potential interaction.

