##### Sample Size Considerations

The study will be adequately powered to detect a clinically important 20% absolute difference in the primary outcome between each intervention arm and usual care and similar 20% difference between the 2 intervention arms (20% has been previously identified by a consensus of Canadian experts as the required minimum clinically important difference for any new hypertension [or any other cardiometabolic] intervention directed at patients with diabetes [53]). Based on pilot data collected in 60 seniors residing in supportive living at two Edmonton sites, only 18% were within the therapeutic range at baseline. Assuming 5% improvement with usual care (related to secular or temporal trends and trial participation or Hawthorne type effects), 20% further improvement with telemonitoring, and a further 20% improvement with telemonitoring + case management, a 2-tailed alpha of 0.05, power of 0.80, the required sample size will be ~80 patients per arm or 240 total. Accounting for ≈20% attrition over 1 year, 100 patients per arm or 300 patients total will be recruited.

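### The primary outcome is worded as a change in a yes/no status, which the named tests for dichotomous outcomes do not fit, so the plan does not fix which variable is tested

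*Protocol article*

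**What the plan says.** Four places in the protocol article bear on the point.

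- **Abstract, Results.** "Within-study-arm change scores will be calculated and compared between study arms". The list that follows names the primary outcome as the "proportion of subjects with a mean 24-hour ambulatory systolic BP in the optimal range", so the abstract places a plain proportion under a heading of change scores.
- **Aim 1, Effectiveness.** "The primary outcome is the 1-year change in proportion of patients with overall 24-hour SBP in the optimal range".
- **Data Analysis.** In the second step, "the 6-month and 1-year mean change from baseline in each outcome will be calculated and compared between study arms", and this is done "using chi-square tests for dichotomous outcomes". The third step models predictors of the 1-year change in an outcome and assigns the primary outcome by name to logistic regression. The initial models adjust for age, sex, SBP and residential site.
- **Sample Size Considerations.** The target is a "20% absolute difference in the primary outcome between each intervention arm and usual care and similar 20% difference between the 2 intervention arms". The pilot figure is that "only 18% were within the therapeutic range at baseline". Improvements of 5, 20 and a further 20 points are assumed, and about 80 patients per arm are required (100 after about 20% attrition). No within-patient correlation and no variance of a change appear.

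**The concern.** In-range status is yes or no. A patient's change from baseline therefore takes three values: -1 (left the range), 0 (same status) or +1 (entered the range). A test for a dichotomous outcome and a binary logistic model cannot be applied to that variable without a further rule, and the article gives none. The tested variable could be in-range status at 12 months, or the individual change compared as a mean between arms, and different sentences of the article point to each.

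The two give the trial different power, and the sample size section gives no sign that the change version was considered. In an open-label trial the primary variable should also not remain open to choice once data are available.

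**Working it through.** **Inputs.** Baseline rate in range, p0 = 0.18 (pilot, Sample Size Considerations). Implied 12-month rates: 0.18 + 0.05 = 0.23 (usual care), 0.23 + 0.20 = 0.43 (telemonitoring), 0.43 + 0.20 = 0.63 (telemonitoring plus case management). The article gives the increments but does not print these three rates. Two-sided alpha 0.05, power 0.80, 80 evaluable per arm. The correlation ρ between baseline and 12-month status is not in the article; it is assumed over a range.

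**1. The plan's own figure.** For two independent proportions with mean p̄, n = [1.96·√(2p̄(1-p̄)) + 0.842·√(p1q1 + p2q2)]² / 0.20².

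- 23% vs 43%: (1.303 + 0.547)²/0.04 gives 86 per arm.
- 43% vs 63%: (1.383 + 0.582)²/0.04 gives 97 per arm.
- 18% vs 38% (usual-care improvement left out): 78.
- 5% vs 25% (the changes treated as if they were proportions): 49.

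The stated figure of about 80 is not reproduced from the implied rates. That shortfall is a separate point. What matters here is that the figure lies nearest to an ordinary comparison of two proportions and contains no change-score calculation. The attrition step reproduces: 80/(1 - 0.20) = 100.

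**2. Power on 12-month status, 80 per arm.** Power = Φ{[0.20·√80 - 1.96·√(2p̄(1-p̄))] / √(p1q1 + p2q2)}.

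- 23 vs 43: (1.789 - 1.303)/0.650 = 0.747, power 77%.
- 43 vs 63: (1.789 - 1.383)/0.692 = 0.586, power 72%.

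**3. Expected contrast on change.** (p1 - p0) - (p2 - p0) = p1 - p2. With equal expected baseline rates under randomisation, p0 cancels and the 20-point contrast is unchanged.

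**4. Variance of individual change.** In each arm, Var = p0q0 + p1q1 - 2ρ√(p0q0·p1q1), with p0q0 = 0.1476. Power = Φ{0.20/√[(Var1 + Var2)/80] - 1.96}.

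For 23 vs 43 at ρ = 0: Var1 + Var2 = 0.1771 + 0.2451 + 2(0.1476) = 0.7174; SE = √(0.7174/80) = 0.0947; 0.20/0.0947 - 1.96 = 0.15; power 56%.

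| ρ (assumed) | 23 vs 43 | 43 vs 63 |
|---|---|---|
| 0 | 56% | 53% |
| 0.2 | 65% | 62% |
| 0.3 | 71% | 68% |
| 0.4 | 77% | not feasible |
| 0.5 | 84% | not feasible |
| *12-month status* | *77%* | *72%* |

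**5. Feasibility.** The share in range at both times, p0p1 + ρ√(p0q0·p1q1), cannot exceed p0. For p1 = 0.63 this gives ρ ≤ (0.18 - 0.1134)/0.1855 = 0.36, so 0.4 and above cannot occur with these margins. For 43 vs 63, change is therefore less powerful at every tabulated correlation that can occur. For 23 vs 43 the break-even is near 0.4.

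**The case against.** The Aim 1 sentence can be read at arm level, as a change in a proportion and not as a patient-level score. On that reading a chi-square test on 12-month status estimates the same 20-point contrast, because randomisation equalises the expected baseline. This stands. A reader might infer that the stated test fails to test the stated endpoint at all; the article does not support that, only that it leaves the variable unfixed.

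A reader might also infer that the primary test would be a chi-square on three change categories, which could reject when both arms change by the same net amount. The article does not prescribe such a test. It reserves chi-square for dichotomous outcomes and names the primary outcome among the dichotomous outcomes for logistic regression.

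Part of the remedy is already present, since the initial logistic models adjust for SBP. But those models are introduced as models for predictors of the 1-year change, so they inherit the same undefined outcome, and the between-arm comparison itself is the unadjusted second step.

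Finally, an article may leave detail to a full protocol or analysis plan. That does not answer the point: the article itself states both the outcome and the test, and the mismatch lies in what it states.

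**Conclusion.** The point holds as a mismatch between outcome wording and test that leaves the primary variable open. It does not show bias or a wrong estimand: the expected contrast is 20 points either way. The consequence is precision. At 80 per arm, 12-month status gives 77% and 72% power. Individual change gives 56% to 84% for 23 vs 43 (ρ from 0 to 0.5) and 53% to 68% for 43 vs 63 (ρ from 0 to 0.3).

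These figures rest on rates implied by the sample size section and on a correlation that the article does not give. It would go too far to say that change always loses power: for 23 vs 43 it equals 12-month status at about 0.4 and exceeds it at 0.5. It would also go too far to state as fact that the trial was sized on 23%, 43% and 63%, since those rates are not printed and do not return about 80 per arm.

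**What to change.** - Define the primary endpoint as 24-hour SBP in the optimal range at 12 months (yes/no).
- Make the primary between-arm comparison a logistic regression or a risk difference on that status, adjusted for baseline 24-hour SBP or baseline in-range status. Adjustment uses the baseline correlation without adding baseline noise. As a rough guide, the residual variance is p1q1(1 - ρ²): for 23 vs 43 at ρ = 0.5, 0.4222 × 0.75 = 0.317, against 0.366 for change and 0.422 unadjusted.
- Drop change scores for binary outcomes; keep them, if wanted, for continuous ones.
- Use the same definition in the abstract, Aim 1, Data Analysis and Sample Size Considerations, and print the 12-month rates assumed for each arm.
- Report moves into and out of range descriptively, separating too high from too low, since avoiding both is the trial's aim.

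The cost is wording in the endpoint and analysis sections. No new data, visits or measurements are needed.

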##### Data Analysis

First, variables will be examined descriptively and graphically, including assessments of temporal trends and tests of normality. Second, the 6-month and 1-year mean change from baseline in each outcome will be calculated and compared between study arms (each intervention arm to the control arm, then between intervention arms) using chi-square tests for dichotomous outcomes and unpaired *t*-tests for continuous outcomes. Third, multivariable predictors of the 1-year change in a given outcome will be identified using appropriately constructed and calibrated logistic regression models for dichotomous outcomes (including the primary outcome) or linear regression models for continuous ones. Initial models will adjust for age, sex, SBP, and residential site (eg, Greater Edmonton Foundation versus Rosedale). Examples of additional covariates that may be examined include sociodemographic variables, comorbidities, baseline medications, primary care physician, and tests of potential interaction.

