## Methods

### Study Design

In this 1-year pragmatic, prospective randomized open label trial with blinded ascertainment of end points, 300 patients will be randomly assigned (1:1:1) to one of 3 study arms (Figure 1): (1) enhanced usual care (in which participants will be given a home monitor but BP teletransmission will not be accessible and case management not available to them); (2) home BP telemonitoring alone; and (3) home BP telemonitoring plus protocolized case management.

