### Randomization

Computer-generated randomization will be performed centrally and independently by the EPICORE center (www.epicore.ualberta.ca) to ensure allocation concealment from all research personnel. Randomization will be stratified by baseline SBP (<140 mmHg versus ≥140 mmHg). Although clinic staff and pharmacist case managers cannot be blinded to allocation status, all outcome assessments will be performed by research assistants working independently from regular clinic staff and the pharmacist case managers.

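### Arms are compared with unadjusted chi-square tests and change-score t-tests although randomisation is stratified on baseline SBP; the planned adjusted model should be named as the primary comparison.

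*Protocol article*

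**What the plan says.** All places are in the protocol article.

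- **Study Design:** "300 patients will be randomly assigned (1:1:1) to one of 3 study arms".
- **Randomization:** "Randomization will be stratified by baseline SBP (<140 mmHg versus ≥140 mmHg"). Which SBP measurement defines the stratum is not stated there.
- **Aim 1, primary outcome:** "The primary outcome is the 1-year change in proportion of patients with overall 24-hour SBP in the optimal range". The upper limit of that range differs between patients aged 65-79 and those aged 80 or over.
- **Data Analysis, second step:** "the 6-month and 1-year mean change from baseline in each outcome will be calculated and compared between study arms", pairwise, "using chi-square tests for dichotomous outcomes and unpaired" t-tests for continuous outcomes.
- **Data Analysis, third step:** "multivariable predictors of the 1-year change in a given outcome will be identified using appropriately constructed and calibrated logistic regression models" for dichotomous outcomes, the primary outcome included, and linear models for continuous ones. "Initial models will adjust for age, sex, SBP, and residential site". Further covariates are given as examples that may be examined.

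The second step is the only one described as a comparison of the arms.

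**The concern.** A factor used to stratify randomisation is balanced across arms by design. If it predicts outcome, a test that ignores it leaves the between-stratum variation in its standard error, although the design has removed that variation from the treatment difference. Intervals are then too wide and the test is conservative.

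Baseline 24-hour SBP and age 80+ raise a related but separate issue. An unadjusted test that ignores them is valid but less precise than it could be. Age 80+ is likely to be prognostic because it sets which range counts as success. For continuous outcomes, subtracting the baseline value is less efficient than regressing on it.

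Two things are at stake. Precision is given up although the data needed to recover it are already collected at baseline. And the plan will produce both an unadjusted and an adjusted result for the primary outcome without naming the one that answers the question.

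**Working it through.** **Inputs from Sample Size Considerations.** 18% in range at baseline; +5 points with usual care, giving 23%; +20 with telemonitoring, giving 43%; a further +20 with case management, giving 63%; two-sided alpha 0.05; power 0.80; about 80 evaluable per arm, 100 after 20% attrition.

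**Step 1. The plan's own figure.** With pooled variance, n per arm = [1.96·√(2p̄q̄) + 0.8416·√(p₁q₁+p₂q₂)]² / d².

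- 23% vs 43%: p̄ = 0.33, 2p̄q̄ = 0.4422, p₁q₁+p₂q₂ = 0.1771 + 0.2451 = 0.4222. (1.303 + 0.547)²/0.04 = 85.6, so 86 per arm.
- 43% vs 63%: p̄ = 0.53, 2p̄q̄ = 0.4982, sum = 0.2451 + 0.2331 = 0.4782. (1.383 + 0.582)²/0.04 = 96.6, so 97 per arm.

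The stated figure of about 80 is not reproduced for either comparison. The attrition step is: 80/0.80 = 100.

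**Step 2. Unadjusted power at 80 per arm.** Power = Φ[(d√n − 1.96√(2p̄q̄)) / √(p₁q₁+p₂q₂)], with d√n = 0.2 × 8.944 = 1.789.

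- 23% vs 43%: (1.789 − 1.303)/0.650 = 0.747, power 77%.
- 43% vs 63%: (1.789 − 1.383)/0.692 = 0.586, power 72%.

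**Step 3. Binary outcome, two-level stratum only.** The article gives no in-range rates by stratum, so a gap g between two equal-sized strata is assumed, the same in both arms. The within-stratum variance sum is the unadjusted sum minus 2(g/2)² = g²/2. For 23% vs 43%:

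- g = 0.20: 0.4222 − 0.02 = 0.4022; SE ratio √(0.4222/0.4022) = 1.02.
- g = 0.40: 0.4222 − 0.08 = 0.3422; SE ratio √(0.4222/0.3422) = 1.11.

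Simulation, 20,000 trials per setting, 80 per arm:

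| Assumed gap | 23 vs 43: chi-square / CMH power | 43 vs 63: chi-square / CMH power | Actual type I error of chi-square |
|---|---|---|---|
| 0 | 78% / 78% | 72% / 72% | 4.6-4.9% |
| 20 points | 79% / 80% | 71% / 73% | 4.2-4.5% |
| 40 points | 81% / 86% | 74% / 80% | 2.7-2.9% |

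CMH keeps its type I error near 4.9% at gaps of 20 and 40 points. The gain in power is about 0 to 6 points.

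**Step 4. Binary outcome, continuous baseline SBP and age 80+.** Assumed, none of it in the article: 24-hour SBP mean 146 and SD 15 mmHg, 40% aged 80 or over, baseline to 12-month correlation 0.4 to 0.7. At 23% vs 43% with 80 per arm, simulated power of the adjusted logistic model is about 82-88%, against about 77% for chi-square: 82 − 77 = 5 to 88 − 77 = 11 points.

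**Step 5. Continuous outcomes.** With equal variances at both times and correlation rho, change-score variance is proportional to 2(1−rho) and ANCOVA variance to 1−rho². Ratio = (1−rho²)/(2(1−rho)) = (1+rho)/2.

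- rho = 0.4: 0.70, so the change-score SE is larger by √(1/0.70) = 1.20.
- rho = 0.7: 0.85, so larger by √(1/0.85) = 1.08.

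Illustration with 5 mmHg (the meta-analysis figure in the Introduction), an assumed SD of 12 mmHg and 80 per arm: at rho = 0.5, power is 75% for the change score and 86% for ANCOVA; at rho = 0.7, 93% and 96%.

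**The case against.** **Adjustment is already planned.** The third step names age and SBP in its initial models and includes the primary outcome. A reader might infer that the protocol ignores baseline SBP altogether or picks all its covariates by search. The text does not support that: a core set is named, and only the additional covariates are open. What stands against the plan is narrower. That step is described as identifying predictors, its SBP term is not tied to the ambulatory value or the stratum, and the stated comparison of arms is the unadjusted one.

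**No validity error is shown.** Correct. A reader might infer bias or too many false positives. Ignoring the stratum causes neither; it makes the test conservative. Unadjusted tests followed by adjusted models are a legitimate, less efficient choice.

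**The power shortfall has another cause.** A reader might infer that the unadjusted test is what takes the trial below 80% power. Step 1 shows that it comes mainly from the figure of about 80 per arm, which does not follow from the stated rates. If the stratum is not prognostic, stratified and unadjusted tests perform alike. For 43% vs 63%, stratifying reaches 80% only at a 40-point gap.

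**The size for the primary outcome is assumption-driven.** Also fair. The values assumed in Step 4 imply 21.5% in range at baseline rather than the pilot 18%, and under 1% below 110 mmHg. The outcome is then nearly one-sided, which favours a linear baseline term. If low readings are commoner, a linear term would gain less.

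**Ranking of analyses may be left to the SAP.** Possibly, but the article does fix a method for comparing arms. The point is about that method, not about missing detail.

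**Conclusion.** The point holds as a matter of efficiency. The article fixes a between-arm comparison less precise than one it already has the data and the models to make, and does not say which result is the treatment-effect estimate.

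The direction is firm. For continuous outcomes the (1+rho)/2 ratio is algebra under equal variances, and below 1 for any rho below 1. The size for the binary primary outcome is not firm: from no gain, if the stratum is not prognostic and is the only covariate, to about 11 points with continuous baseline SBP and age 80+ at the upper end of the assumed correlations. Adjustment helps a trial with little power to spare, but it does not repair the sample-size calculation, which is a separate matter.

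**What to change.** In Data Analysis, make the adjusted model the primary between-arm analysis, with covariates fixed in advance.

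- **Binary outcomes:** logistic regression on treatment, randomisation stratum, baseline 24-hour SBP and age 80+ (yes/no), reported as a standardised risk difference with 95% CI.
- **Continuous outcomes:** ANCOVA of the 12-month value on treatment, its own baseline value and stratum.
- **Support:** keep the chi-square and t-tests as unadjusted analyses.
- **Exploratory:** label any search over further predictors or interactions as such.

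Say also which SBP measurement defines the stratum, so that the model term matches the randomisation.

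The cost is a change of wording and a little programming. The covariates are already in the baseline data collection, and no extra patients or visits are needed.
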